## Material and methods

### Participants

All patients consecutively admitted to the Neurorehabilitation Unit at the ICS Maugeri (Bari, Italy) with Vegetative State (VS) or minimally conscious state (MCS) [45] will be assessed. Our hospital is a reference centre for patients with severe acquired brain injury; a letter will be sent to the acute hospitals from which patients come with the aim of informing them of the research project. Inclusion criteria will be the following: clinical diagnosis of VS or MCS according to standardised clinical diagnostic criteria, traumatic, vascular, or anoxic aetiology. The assessment will rely on neuropsychological instruments as well as on Magnetic Resonance Imaging (MRI) and Computed Tomography (CT) evidence. Exclusion criteria will be: presence of pacemaker or metallic cerebral implant, craniolacunia, ventricular peritoneal shunt, age <18 years, auditory injury as evaluated by anamnesis, history of neurological and psychiatric disease, previous stroke, use of alcohol or drugs, premorbid dementia. As recommended, a period of observation will be conducted for one week [46] twice a day by four independent examiners (physician, neuropsychologist, speech therapist and physiotherapist).

Before the enrolment, patients will undergo neurophysiological recordings, namely Brainstem Auditory Evoked Potentials (BAEP) to assess the integrity of the central auditory pathway. Patients will be divided according to the brain aetiology of their pathological condition. Caregivers will also be assessed to investigate the emotional and psychological burden and psychophysiological condition.

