### Sample size determination

The effect size to be expected is uncertain as no study so far has implemented a combined intervention of music and electrical stimulation in DOC patients. We assume it to be in the medium-to large range (i.e., Cohen’s d between 0.5 and 0.8). We aim to achieve 80% power (*f* = 0.30) in a repeated-measures analysis of variance (*a* = 0.05, power (1-b) = 0.80) with condition as between-subject factor (tES combined with music stimulation vs. sham stimulation, and noise vs. music stimulation and sham stimulation), and time (pre-intervention, post-intervention and post-placebo), as within-subject factor. Power calculations (using G* Power 3) indicate that a valid sample size of *n* = 10 per group will result in 80% statistical power if the effect is *d* = 0.68, which is in the medium-to-large range. This results in a total sample size of *n* = 30.

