### Experimental design and procedures

The experimental paradigm is one of the main strengths of the study, as a randomized cross-over design will be used in this trial, including a treatment condition with electric brain stimulation combined with music listening and a placebo condition with sham brain stimulation combined with noise listening. The randomization of the participants to be included in each group will be done using the software “Research Randomizer” (www.randomizer.org). The randomization procedure will be performed by an independent researcher unrelated to the study. The randomization file will be saved in a password-protected online database. This independent researcher will enrol participants and will assign the patients to intervention groups. Both patients and examiner will be fully blinded.

Assessment times of outcome measures will be conducted at admission (T_0_), after the first weeks of post-intervention or post-placebo (T_1_), and after the second two weeks of post-intervention or post-placebo (T_2_) (Fig 1). Patients will be randomized into three groups depending on the order of the stimulation or placebo conditions:

Stimulation-Placebo: Patients receiving tES combined with music stimulation for 2 weeks, 1 week of wash out, then sham stimulation combined with noise (placebo) for other 2 weeks.Placebo-stimulation (combined tES and music): Patients receiving sham stimulation and noise (placebo) for the first 2 weeks, then 1 week wash out, and finally tES and music stimulation for other 2 weeks.Music-placebo: Patients receiving music stimulation and sham stimulation for 2 weeks, 1 week of wash out, then sham stimulation and noise (placebo) for another 2 weeks.

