### Neurophysiological, neuropsychological and clinical primary outcomes

For obtaining the neurophysiological primary outcome measures, we will compute the power spectra of frequency bands from continuous EEG to assess the residual neuroplastic processes existing in DOC state, and we will then evaluate the putative modulation of these processes by the combined intervention of music and brain stimulation in a randomized cross-over design. EEG data will be acquired using a Galileo Mizar Plus medical device including 26 monopolar electrode channels, 16 bipolar electrode channels and 10 additional channels used for EEG recordings.

For the EEG measures, we will use the following paradigms:

Rest for 10 minutes with annotation on whether patients keep eyes open or closed for measuring the power spectra of frequency bands from the continuous EEG.Free listening to the morning musical playlist as used in the music stimulation condition for measuring the power spectra of frequency bands and the evoked N100 responses from the continuous EEG.

For assessing the clinical conditions of DOC patients, the following scales will be used.

Glasgow Outcome Scale–Extended (GOS-E) [53]: A global scale for functional outcome that rates patient status in eight categories according to the disability.Coma Recovery Scale—Revised (CRS-R) [54]: A tool which includes the current diagnostic criteria for coma, vegetative state, and the MCS, and allows the patient to be assigned to the most appropriate diagnostic category.Disability Rating Scale (DRS) [55]: A scale that evaluates the functional changes in a rehabilitation setting. The DR Scale consists of 8 items divided into 4 categories: Arousal and awareness; cognitive ability to handle self-care functions; physical dependence upon others; psychosocial adaptability for work, housework, or school.Rancho Levels of Cognitive Functioning (LCF) [56]: A scale that assesses cognitive functioning in post-coma patients, classifying them in one of eight level: No response; Generalized; Localized; Confused-agitated; Confused, inappropriate, non-agitated; Confused-appropriate; Automatic-appropriate; Purposeful-appropriate.

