### Data analysis

The SPSS 23.0 statistical software will be used for the data analysis. All the statistical hypotheses will be tested by two-side test, with statistically significant test level set at 0.05 and the confidence interval estimation to 95%.

The aim of our study is to evaluate the effects of the treatments in the various patient groups on the primary and secondary outcomes. Descriptive analysis of the data will allow us to identify the characteristics of the groups. Comparison of demographic and clinical characteristics of the groups will be performed using one-way ANOVA for continuous variables and the Chi-square test for categorical variables. Considering the crossover and longitudinal aspects, primary analyses will focus on behavioural changes at group level, comparing the treatments. Moreover, at the individual level, we will analyse the differences between pre-treatments and post treatments data.

As for the primary outcomes, we will measure the effects of the intervention on the following measures (two neurophysiological and two clinical and behavioral): (i) power spectra of frequency band extracted from the EEG recordings; (ii) auditory evoked responses, extracted from the EEG recordings; (iii) behavioural responses of DOC patients, measured through CRS-R.

Baseline characteristics and carryover effect will be analysed between the three sequences using ANOVA and chi-square test. By including the order of intervention as a covariate, we aim to determine whether the sequence in which participants receive the interventions impacts the observed outcomes. To assess the presence and magnitude of the washout effect, we plan to incorporate appropriate statistical methods into our analysis, such as comparing outcomes during the washout period to those observed during active treatment phases. To this end, we will use repeated measures ANOVA considering time (before, during, and after the washout) as the independent variable, with behavioral measurements as the dependent variables.

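### The CRS-R baseline is set at one time point, at admission, while a pre-treatment week of twice-daily examination has no stated role in the analysis; a mean over the end of that week would be a more precise baseline

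*Protocol article*

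**What the plan says.** The Participants section, after the eligibility criteria, plans that "a period of observation will be conducted for one week [46] twice a day by four independent examiners". It lists four professional roles and names no instrument for these sessions.

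Under Experimental design and procedures, the text reads "Assessment times of outcome measures will be conducted at admission (T_0", and T1 and T2 follow at the ends of the two treatment periods. The Sample size determination section has one pre-treatment level in its model: "time (pre-intervention, post-intervention and post-placebo), as within-subject factor".

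The Data analysis section lists among the primary outcomes "behavioural responses of DOC patients, measured through CRS-R", and adds that "at the individual level, we will analyse the differences between pre-treatments and post treatments data". It also plans repeated-measures ANOVA with post-hoc paired t-tests for level of consciousness. The outcomes section says of the CRS-R that it "allows the patient to be assigned to the most appropriate diagnostic category".

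No section mentions the observation week again.

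**The concern.** Responsiveness in patients with disorders of consciousness can vary from one session to the next. If the baseline is one examination, its session-to-session noise passes in full into every change from T0. The protocol already schedules repeated pre-treatment examinations by available staff, so averaging could reduce that noise without an extra visit. With 10 patients per group, even a modest loss of precision matters.

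There is also a difficulty of timing. If the week follows admission, as its place in the section on admitted patients suggests, a T0 taken at admission cannot summarise it. If T0 does come from that week, the words placing it at admission are wrong. Either way, the text does not fix how the baseline of a primary outcome is obtained.

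**Working it through.** **The plan's own figure.** The sample size section states "We aim to achieve 80% power (*f* = 0.30) in a repeated-measures analysis of variance (*a* = 0.05, power (1-b) = 0.80", with 10 per group and 30 in total. In a noncentral F calculation for a group-by-time interaction, λ = f²·N·m/(1−ρ), with df₁ = (k−1)(m−1) and df₂ = (N−k)(m−1). Here k is the number of groups, m the number of time points and ρ the correlation between time points. Taking k = 3, m = 2, f = 0.30 and an assumed ρ = 0.5 gives λ = 0.09 × 30 × 2/0.5 = 10.8, df 2 and 27, and power 0.800. So N = 30 reproduces as three groups by two times. With the three time points that the section names, the same inputs give power 0.887 at N = 30.

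**Amount of pre-treatment observation.** Two sessions a day is 14 sessions over seven days, or 10 over five. The last three days give 3 × 2 = 6 sessions.

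**Inputs for the gain.**
- From the protocol: d = 0.68, 10 per group, two-sided testing ("All the statistical hypotheses will be tested by two-side test") at 0.05.
- Assumed, because the article gives no figure: d is in SDs of a single rating; the correlation between single T0 and T1 ratings is 0.5; single-rating reliability r is 0.6, 0.7 or 0.8; T0 would otherwise be one rating; the sessions yield CRS-R totals.
- s is the share of session noise common to the whole week, which averaging cannot remove. It is set to 0 or 0.5.

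**Formulas**, with single-rating variance 1 and p sessions averaged:
- Baseline variance: v = r + (1−r)·[s + (1−s)/p]
- Change-score variance: 1 + v − 2 × 0.5 = v
- Residual variance with baseline as covariate: 1 − 0.25/v

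Example, r = 0.7 and p = 6: with s = 0, v = 0.7 + 0.3/6 = 0.75 and the covariate-adjusted variance is 1 − 0.25/0.75 = 0.667. With s = 0.5, v = 0.7 + 0.3 × (0.5 + 0.5/6) = 0.875 and the adjusted variance is 0.714. With one rating (p = 1) the values are 1.00 and 0.75.

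**Power** (noncentral t, 10 against 10; df 18 for change, 17 with covariate):

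| Baseline | r | v | Change score | Baseline as covariate |
|---|---|---|---|---|
| One rating | any | 1.000 | 30% | 38% |
| 6 sessions, s = 0 | 0.6 | 0.667 | 42% | 44% |
| | 0.7 | 0.750 | 38% | 42% |
| | 0.8 | 0.833 | 35% | 40% |
| 6 sessions, s = 0.5 | 0.6 | 0.833 | 35% | 40% |
| | 0.7 | 0.875 | 34% | 40% |
| | 0.8 | 0.917 | 32% | 39% |

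Change-score variance therefore falls by 17-33% with independent session errors, and by 8-17% with half the noise shared. Using all 14 sessions adds little: at r = 0.7 and s = 0, v falls only from 0.750 to 0.721.

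**Reach.** The T1 versus T2 contrast within a patient does not involve T0, so a better baseline does nothing for an unadjusted comparison of the two periods. The later pre/post comparisons in the Data analysis section concern EEG measures and are not affected.

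**The case against.** A reader might infer that repeated CRS-R data are collected and then discarded in favour of a single rating. The documents do not support that. No section says that T0 is one examination, that the sessions are scored with the CRS-R, or that any scores go unused. The week stands among diagnosis and eligibility, and the description of the CRS-R as a diagnostic tool does not show that it is the instrument used then. A condensed article may also leave such detail to the full protocol. This objection stands against the stronger reading. It does not remove the mismatch in the text, which fixes T0 at admission and gives the week no analysis role.

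The 10-against-10 test is not the planned analysis, which is a three-group repeated-measures ANOVA with crossover elements. The power figures above only illustrate the size of the gain. Sessions hours apart, under the same drug treatment, plausibly share some error, so the lower rows of the table deserve as much weight as the upper ones.

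An averaged baseline has costs of its own. If T1 and T2 are rated by one role and the baseline by four, differences between raters enter the uncontrolled pre/post tests. A six-session mean set beside single T1 and T2 ratings also gives unequal variances across the time factor. Both points stand, and the fix has to deal with them.

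Finally, a mean over several days lags behind a recovering patient. That is true, but if the week follows admission, an admission score lags further than a mean over the last three days.

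**Conclusion.** The point holds as an inexpensive improvement and a needed clarification. The article sets the CRS-R baseline at admission, schedules a week of repeated examination before treatment, and does not connect the two. It does not establish that usable data are being thrown away.

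Under the stated assumptions, a six-session baseline would raise illustrative two-group power by about 2 to 12 percentage points on change scores (30% to 32-42%) and by about 1 to 6 points with baseline as a covariate (38% to 39-44%). The size depends on reliability, on the T0-T1 correlation and on how much session noise is shared, none of which the article gives. It applies only to contrasts that use T0.

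**What to change.** 1. Reconcile Participants with Experimental design and procedures: state when T0 falls relative to the observation week, whether the week's sessions are scored with the CRS-R, and whether T0 is one examination or several.
2. If the sessions are not already scored, have the scheduled examiners complete the CRS-R at each.
3. Pre-specify the baseline for the primary CRS-R analysis as the mean over a fixed final part of the week, for example the last three days (six sessions). Use the mean and not the best score, so that the baseline is not raised relative to T1 and T2. Keep the admission score as a descriptive value.
4. Preferably enter this baseline as a covariate, with T1 and T2 as the outcomes. The baseline is then no longer a level of the time factor, which avoids the unequal variances. The article already plans covariates in its ANOVAs for drug treatment.
5. Take the baseline ratings from the same examiner role or roles that rate T1 and T2, so that the rater mix does not enter the pre/post change.

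The cost is wording and data entry, plus completion of the scale by existing examiners if it is not already done. No extra visit or staff is needed. If the baseline stays a level of the time factor in the repeated-measures ANOVA, the unequal variances have to be allowed for. If the rater roles cannot be matched, the uncontrolled pre/post tests should be read with that caution.

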A further group of rehabilitation strategies for brain-lesioned patients, including DOC patients, consists of neuromodulation aimed to alter the physiology of the neural circuits responsible for the behaviour under investigation. Among several neuromodulation approaches, there are pharmacological interventions (e.g., amantadine hydrochloride) [29], deep brain stimulation (for a review see [30]), and Non-Invasive Brain Stimulation techniques (NIBS) [31]. NIBS exists in various forms, although one of the most adopted in clinical settings is transcranial electrical stimulation (tES). This technique consists of delivering a small (1–2 mA) current via two electrodes placed on the scalp. According to the stimulation parameters, tES affects neural excitability and has plastic effects (mediated by NMDA-receptors) [32]. These currents, cathodal (-) or anodal (+), generate an electric field that can modulate spontaneous neural activity by interfering with the membrane potential of the underlying neuronal compartments by inducing, respectively, hyperpolarization (inhibiting effect) or depolarization (facilitating effect) [33]. Importantly, the induced changes become more stable and long-lasting (i.e., aftereffects) when stimulation is repeated several times [34]. Key targets for stimulation in the neurocognitive domain are the dorsolateral prefrontal cortex (DLPFC), especially in working memory, attention, and executive functions, and the posterior parietal cortex (PPC), which plays a critical role in visual spatial perception and attentional processes [35]. Several tES studies show improvements in clinical (e.g., GCS, CRS-R, cognitive, motor) and surrogate (i.e., EEG, TMS, fMRI) outcomes of patients with DOC [36–38], for a review see Kuo et al. [39], although this effect is more evident among MCS patients rather than among unresponsive wakefulness syndrome patients (VS/UWS) [40]. NIBS is, thus, considered a useful tool in the rehabilitation of clinical populations such as patients with DOC [41]; for instance, tES has been used as a potential adjuvant treatment to improve symptoms in patients with hemispatial neglect after stroke [42]. However, there is an increasing understanding that patients do not homogeneously respond to NIBS]. This might be ascribed to the fact that the methodology adopted in tES studies is characterised by a large variability as concerns stimulation parameters, participant characteristics as well as the characteristics of associated rehabilitation treatment.

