
With this study we propose a novel rehabilitation protocol that combines music-based intervention and NIBS in neurological patients aimed to (i) assess the residual neuroplastic processes existing in DOC state, and (ii) evaluate the putative modulation of these processes by a non-pharmacological 2-weeks intervention combining electric (tES) and auditory (music) stimulation. The musical stimulation will consist of musical pieces that vary in familiarity and complexity (from pieces chosen from the favourite ones for the patient to novel pieces following classical tonal style up to atonal pieces). We hypothesize that tES, altering the physiology of neural circuits, can increase the plastic effect of music stimulation and thus increase the responsiveness of the patient. As far as we know, there are no studies in the literature that have evaluated the effectiveness of the association of these treatments in DOC patients Furthermore, an additional novel aspect will be the use of autobiographical music, hence emotionally relevant to the patients.

In addition, we also want to ascertain the influence of this rehabilitation protocol on caregiver’s burden and psychological distress, since acquired brain injury has an important impact on physical, psychological, social and also financial conditions of caregivers; their entire life is modified in order to take care of the patient, causing a strong emotional burden, with high levels of psychophysiological distress, depression, anxiety and a more complex symptomatology called prolonged grief disorders [43, 44]. In this regard, an aim of this study is to evaluate the caregiver’s psychological burden both before and post rehabilitation treatment in order to assess the effect of music stimulation and brain stimulation also on caregiver’s emotional condition.

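### VS and MCS patients are enrolled together and tES is said to work better in MCS, yet this diagnosis is named in neither allocation nor analysis, leaving a between-patient contrast of 10 versus 10 open to chance imbalance

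*Protocol article*

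**What the plan says.** All statements are from the protocol article.

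- **Who enters (Participants):** "clinical diagnosis of VS or MCS according to standardised clinical diagnostic criteria, traumatic, vascular, or anoxic aetiology". The same section adds "Patients will be divided according to the brain aetiology of their pathological condition" and does not say whether this division serves allocation, analysis or description.
- **Expected response (Introduction):** of tES in disorders of consciousness, "this effect is more evident among MCS patients rather than among unresponsive wakefulness syndrome patients (VS/UWS". The Introduction also describes opposite slow-band and fast-band EEG patterns in patients without preserved consciousness and in MCS.
- **Hypothesis (Introduction):** "We hypothesize that tES, altering the physiology of neural circuits, can increase the plastic effect of music stimulation".
- **Allocation (Experimental design and procedures):** "The randomization of the participants to be included in each group will be done using the software" Research Randomizer, operated by an independent researcher. Strata and blocks are not mentioned. Of the three sequences, two contain tES with music. The third reads "Patients receiving music stimulation and sham stimulation for 2 weeks, 1 week of wash out", followed by placebo.
- **Adjustment:** drug treatment and doses (Music stimulation) and order of intervention (Data analysis). Baseline characteristics are to be compared across the sequences by ANOVA and chi-square.
- **Stratification:** the word appears only under Ethical considerations, for stroke patients whom this article does not cover.

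**The concern.** By the protocol's own account, VS/MCS status bears on the response to tES. It is also closely tied to two primary outcomes: CRS-R is the scale that assigns the diagnostic category, and the slow and fast EEG bands separate the two diagnoses.

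A cross-over normally protects against such a factor because each patient is compared with himself or herself. That protection covers tES with music against placebo. It does not cover what tES adds to music, because no listed sequence gives one patient both active conditions. That question is answered by comparing different patients, 10 against 10 in the first period. At that size a chance excess of MCS patients in one group can enlarge or shrink the apparent add-on effect, and nothing stated in the plan limits or corrects for it.

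**Working it through.** **Inputs from the protocol:** 30 patients, 10 per group, f = 0.30, d = 0.68, two-sided 0.05. **Assumptions:** the MCS share (30-70%) and the VS/MCS difference in change, D (0.5 to 1.5 SD). The article gives neither.

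**1. The plan's own figure.** The stated basis is "We aim to achieve 80% power (*f* = 0.30) in a repeated-measures analysis of variance (*a* = 0.05, power (1-b) = 0.80". For the group-by-time interaction, lambda = f² × N × m / (1 − rho), with (k − 1)(m − 1) and (N − k)(m − 1) degrees of freedom. With k = 3, N = 30, m = 2 and rho = 0.5, lambda = 0.09 × 30 × 2 / 0.5 = 10.8 and power = 0.80. With the three time points stated, N = 30 results for rho of about 0.38 to 0.44. So N = 30 is reproducible, although rho is not given. The present point does not depend on it.

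**2. How often the groups differ.** With M MCS patients among 30 and groups of exactly 10, the probability of a split a/b/c is C(10,a) C(10,b) C(10,c) / C(30,M). Summing over splits in which two given groups differ by at least 3, or at least 4:

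| MCS patients (M) | differ by 3 or more | differ by 4 or more |
|---|---|---|
| 9 or 21 (30% or 70%) | 0.23 | 0.09 |
| 12 or 18 (40% or 60%) | 0.26 | 0.11 |
| 15 (50%) | 0.27 | 0.12 |

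**3. What an imbalance of 3 does.** Shift = (3/10) × D.

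- D = 0.5: 0.15 SD, which is 0.15/0.68 = 22% of the planned d
- D = 0.8: 0.24 SD, or 35%
- D = 1.5: 0.45 SD, or 66%

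**4. Error rate.** Simulation with 50% MCS and no tES effect:

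| D | type I error, all trials | given imbalance of 3 or more | same trials, adjusted for diagnosis |
|---|---|---|---|
| 0.8 | 0.05 | 0.08 | about 0.05 |
| 1.5 | 0.05 | 0.12 | about 0.05 |

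**5. Precision.** Without stratification or adjustment, the SD of the 10-versus-10 contrast is √[0.2 × (1 + D² × 0.25 × 30/29)] at 50% MCS. This gives 0.46 for D = 0.5, 0.48 for D = 0.8 and 0.56 for D = 1.5. With balance and adjustment it is √0.2 = 0.45. The gain is small at D = 0.5 and clear at D = 1.5.

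**6. Would the planned baseline test notice?** With 15 MCS patients, chi-square = 2 × Σ(count − 5)² / 5 on 2 df. A 7/5/3 split gives 2 × (4 + 0 + 4)/5 = 3.2, p = 0.20. A 7/4/4 split gives 2 × (4 + 1 + 1)/5 = 2.4, p = 0.30. Neither would be flagged.

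**The case against.** The strongest reply is that the article condenses a fuller protocol. Strata, blocks and covariates may be specified there, and the silence here proves nothing. This stands in part. A reader might infer that allocation is simple, but the article does not say so. Fixed groups of 10 point to some restriction, since unrestricted allocation gives 10/10/10 in only about 3% of trials, and the probabilities above already assume exact tens. What remains is that the article does name a division and covariates, and omits the one factor it singles out as related to response.

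Four further readings go too far, and the objections to them hold.

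- **Confounding.** Randomisation keeps the overall type I error near 5%. Diagnosis and T0 CRS-R are recorded, so an imbalance can be separated from treatment by adjustment.
- **Differences in level.** One could multiply 0.3 by an assumed 4 to 8 CRS-R points between VS and MCS and report a shift of 1.2 to 2.4 points. The planned repeated-measures analysis includes T0, so a stable difference in level largely cancels. The same applies to the opposite EEG patterns. Only a difference in change matters.
- **A false tES effect from effect modification.** If tES does nothing, a larger tES effect in MCS cannot create one. A false effect requires MCS patients to change more without tES, which is assumed here. If tES does work, the Introduction's statement alone implies that the estimate moves with the MCS share of the tES group.
- **Aetiology as the wrong factor.** Nothing in the document shows aetiology to be less prognostic than VS/MCS, nor that it is meant as an allocation stratum.

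It is also fair to note that 20 patients receive tES with music and that every patient has a placebo period. Comparing active-minus-placebo differences between sequences removes stable patient differences. It does not remove a diagnosis-related difference in change, and the patients compared are still different people.

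Finally, the Brain stimulation text describes one real and one sham week, which might suggest a within-patient contrast. The listed sequences do not contain it, and no assessment is listed between such weeks. Those passages need reconciling.

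**Conclusion.** The point holds in a limited form. VS and MCS are enrolled together, the protocol says tES works more evidently in MCS, and this diagnosis is named in neither allocation nor adjustment. The add-on effect of tES is estimated between different patients. An imbalance of 3 or more MCS patients between two given groups has a probability of roughly one in four, so about three trials in four avoid it. When it occurs, the contrast moves by 0.15 to 0.45 SD, and the planned baseline test would often not flag it.

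The harm is lost precision and a realised result that is hard to interpret, not systematic bias. The size rests on the assumed MCS share and the assumed VS/MCS difference in change. If that difference were near zero, the no-tES shift would vanish, and only the modification of a real tES effect would remain.

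**What to change.** - Generate the allocation list within two strata, VS and MCS, using the diagnosis at the end of the one-week observation, with varying block sizes.
- Prespecify VS/MCS, or baseline CRS-R, as a factor or covariate in the primary group comparison.
- State whether the division by aetiology is for allocation, analysis or description.
- If enrolment has begun, leave the list alone and prespecify the adjustment before outcomes are analysed.

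The data are already collected: diagnosis is an inclusion criterion and CRS-R is measured at T0. The cost is a new list, one degree of freedom, and slightly more predictable allocation in small blocks, which varying the block size limits.
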